### Setting

The setting is eight primary care centres in Málaga and Almería, Spain.

### Study variables

#### Individual variables/first-level variables (patients)

The primary outcome is performance of the correct inhalation technique by patients (evaluated through a specific step-by-step test for each inhaler). This test has been specially designed for this study on the basis of SEPAR recommendations [4]. We consider the correct inhalation technique to be used when all steps have been performed correctly.

Secondary outcomes are functional status as measured by forced spirometry [27], dyspnoea index as measured using the Basal Dyspnea Index [28] and the modified Medical Research Council dyspnoea scale [29] and health-related quality of life as measured using the St George’s Respiratory Questionnaire (SGRQ) [30].

Independent variables are age, sex, education level, co-morbidities, COPD diagnosis duration, mental and/or cognitive status (Mini Mental State Examination [31]), types and number of inhalers, previous training received in use of the inhalation techniques and prescribed treatment for COPD.

#### Group variables/second-level variables (GPs)

Group and second-level variables are correct performance of the inhalation techniques by GPs (evaluated using a specific step-by-step test for each inhaler, described below), knowledge about COPD and its treatment (evaluated by using a questionnaire specially designed for this study and based on COPD PAI [16], Spanish COPD Guidelines [15] and GOLD guidelines [2]).

#### Independent variables

The independent variables are age, sex, education level and access to the COPD clinical practice guidelines.

### Statistical analysis

#### General

A descriptive statistical analysis will be performed for all study variables. We will calculate the means, medians and standard deviations for quantitative variables and the absolute and relative frequencies for qualitative variables. The 95 % confidence interval will be applied. The analysis will be done according to the intention-to-treat principle. The baseline comparison will be made between the main variables that we expect to be related to the primary outcome using the χ^2^ test or analysis of variance (ANOVA).

At the first level, the between-group comparison for the primary outcome will be explored using the χ^2^ test. Relative risk reduction, absolute risk reduction and NNT will be calculated. Inferences for secondary outcomes will be made using ANOVA or the χ^2^ test.

Finally, a logistic regression model will be used for the primary outcome (performance of the right inhalation technique [yes or no]), considering the intervention as the predictive variable and the rest of the independent measures as the possible modifying factors. We will use the usual 5 % significance level (α = 0.05) and the SPSS version 15.0 statistical software package (SPSS, Chicago, IL, USA) to run the proposed analysis.

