### Participants

A total of 267 patients diagnosed with COPD and receiving inhalation therapy will be selected from 20 general practices in 8 primary care centres in Málaga and Almería, Spain. This sample size is enough to detect a 25 % difference between groups regarding the right performance of inhalation technique, with a power of 80 % and a confidence level of 95 %. The sample size was adjusted according to the standard criteria for cluster randomised trials, using the design effect (DE) of 2.3. The DE was calculate as follows: DE = 1 + (*n*_c_ – 1) × ICC (where *n*_c_ is the mean number of individuals in the cluster and ICC is the intra-cluster correlation coefficient). The ICC in the present work was considered to be 0.1, and the mean cluster size was assumed to be 10 [24–26]. A potential loss of 40 % was estimated. Therefore, inclusion of 267 patients and 20 GPs will be required, with all of them signing consent forms to participate in the study.

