#### Multi-level analysis

ICCs will be determined and published for all primary outcome variables to assist future research. Potential confounders will be compared between groups to confirm that the randomisation has provided the appropriate balance.

The effect of the intervention on outcomes measured on a continuous scale (such as SGRQ score) will be estimated and tested using mixed model ANOVA in which time and treatment group will be fixed effects and GP and subject will be random effects. The effect of the intervention on the dichotomous variables will be analysed using generalised estimating equations with a logistic link and a model structure that is analogous to that described above.

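### The primary outcome has unadjusted and cluster-adjusted analyses with none named as decisive; if the χ² test decided, its true error would be about 13–16%, not 5%

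*Protocol article*

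**What the plan says.** The unit of randomisation is the GP: 10 control and 10 intervention (Recruitment and randomisation). The sample size (Participants) allows for clustering: "The ICC in the present work was considered to be 0.1, and the mean cluster size was assumed to be 10".

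Two neighbouring subsections then describe the comparison between arms.

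- **General.** At patient level, "the between-group comparison for the primary outcome will be explored using the" χ² test, followed by relative and absolute risk reduction and NNT. Secondary outcomes are inferred on by ANOVA or χ². Then "a logistic regression model will be used for the primary outcome", with the intervention as predictor and the other independent measures as possible modifiers. The GP appears in none of these. The error level is set here: "We will use the usual 5 % significance level".
- **Multi-level analysis.** "The effect of the intervention on the dichotomous variables will be analysed using generalised estimating equations with a logistic link", with a structure like that of the mixed model for continuous outcomes, in which "time and treatment group will be fixed effects and GP and subject will be random effects".

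Correct technique is a yes/no outcome, so the second subsection covers it too, although only the first refers to the primary outcome when it assigns a method. No sentence ranks the two sets.

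**The concern.** Patients of one GP share the trained or untrained doctor, so their outcomes are correlated; the plan's own ICC says so. A χ² test, an ANOVA or a logistic regression without a GP term counts each patient as independent information on the arm difference. Standard errors are then too small.

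The primary outcome thus has three planned analyses, two of which do not respect the design. The unadjusted test can be significant when the adjusted one is not, and the text allows either to be reported as the result. Secondary outcomes have the same double provision. The answer also has a consequence: under Study limitations, training of the control GPs after the trial depends on a significant benefit in patients, and the text does not say which test establishes it.

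**Working it through.** **Inputs from the protocol article.** ICC 0.1, mean cluster size 10, stated design effect (DE) 2.3, 267 patients, 20 GPs and 40% loss (Participants); 10 GPs per arm (Recruitment and randomisation); α = 0.05 (General). Assumed, because not stated: two-sided testing, equal cluster sizes, loss spread evenly over GPs, and the event rate.

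**1. The plan's own design effect.** Its formula is DE = 1 + (m − 1) × ICC. With m = 10: 1 + 9 × 0.1 = 1.9, not 2.3. A DE of 2.3 needs m = 14, which exceeds even 267/20 = 13.35 recruited per GP. That mismatch is a separate point; here it only determines which DE is a fair input.

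**2. Patients retained per GP.** 267 × 0.6 = 160, and 160/20 = 8, so DE = 1 + 7 × 0.1 = 1.7.

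**3. True error of an unadjusted test.** Ignoring clustering understates the standard error by √DE, so the true two-sided error is 2 × [1 − Φ(1.96/√DE)].

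| Patients per GP | DE | √DE (interval too narrow by) | 1.96/√DE | True error |
|---|---|---|---|---|
| 8 (after 40% loss) | 1.7 | 1.30 | 1.50 | 13.3% |
| 10 (assumed in the plan) | 1.9 | 1.38 | 1.42 | 15.5% |
| 13.35 (no loss) | 2.235 | 1.49 | 1.31 | 19.0% |
| 14 (stated DE) | 2.3 | 1.52 | 1.29 | 19.6% |

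**4. Check by simulation.** Beta-binomial data with no arm effect, ICC 0.1, 10 GPs per arm, event rates 0.15, 0.25 and 0.5, 100,000 runs per setting. The χ² test rejected in 12.9–13.7% of runs at m = 8, 15.6–16.8% at m = 10 and 19.6–19.9% at m = 14, in line with the formula.

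**5. What adjustment achieves.** Over m = 8 to 14 in the same simulations:
- a cluster-level t-test (18 degrees of freedom) rejected in 4.7–5.1% of runs;
- a cluster-robust (sandwich) z-test without small-sample correction, standing in for the planned GEE, rejected in 7.7–8.1%.

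Adjustment removes most of the inflation, and a small-sample method removes the rest.

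The logistic regression was not simulated. Without a GP term it rests on the same independence assumption, so inflation of a similar order is expected, but the figures above are for the χ² test.

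**The case against.** The strongest reply is that a cluster-adjusted analysis is already planned. The Multi-level analysis subsection covers every dichotomous variable, and the primary outcome is one. The χ² comparison is only to be explored, whereas the GEE is what the intervention effect will be analysed with; a first look at patient level followed by the proper model is a plausible reading. The article is also condensed, and a fuller plan may rank the analyses.

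Much of this stands. A reader might infer that the trial has no valid primary analysis and that its false-positive rate simply is 13–20%. The document does not support that: the inflated rate is the trial's only if the unadjusted tests decide. The upper end is weak too, since 19.6% needs a DE that ICC 0.1 and 10 patients per GP do not produce. Nor are the risk reductions and NNT wrong in themselves: their point estimates need no independence assumption, only their intervals do, and the interval method is not given. For continuous secondary outcomes the mixed model with GP as a random effect is likewise already there.

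What does not stand is that the wording settles the matter. The softer verb covers the χ² sentence alone. The logistic model is to be used for the primary outcome, in the paragraph that sets the 5% level, and the unadjusted secondary tests are presented as inference. This is not detail left to another document: the article states methods that do not fit its own design beside methods that do.

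**Conclusion.** The concern holds as a conflict between two subsections, not as the absence of a cluster-adjusted analysis. Both primary and secondary outcomes have unadjusted and adjusted between-arm analyses, and none is named as confirmatory.

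Should the χ² test decide, the plan's inputs imply a true two-sided error of about 13% (8 retained per GP) to 16% (10 per GP), and intervals too narrow by a factor of 1.30 to 1.38. The figures of about 20% and 1.52 apply only if the stated DE of 2.3 is accepted. All of this is conditional on the ICC of 0.1, equal cluster sizes and two-sided testing. It needs correcting before analysis, because the plan otherwise leaves open which p-value is the result.

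**What to change.** - Name the GEE of the Multi-level analysis subsection as the single primary analysis of correct technique, with GP as the cluster and a stated small-sample correction for 20 GPs. A cluster-level t-test would also serve. Without such a correction the error would stay near 8%.
- Use the models of that subsection for the secondary outcomes.
- Take the confidence intervals for the risk difference, relative risk and NNT from a cluster-adjusted analysis.
- Keep the χ², ANOVA and unadjusted logistic results of the General subsection as description, without a role in the conclusion.

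Only the wording of the analysis changes; design, recruitment and data collection do not. The cost is that p-values and intervals become less favourable than the unadjusted ones.

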##### Recruitment

For recruitment, potentially eligible patients will be identified through a search of practise electronic records by research assistants. Eligible patients will receive a brief explanation of the intent of the study by phone, and, if they are interested, they will be given an appointment at their primary care centre for a more detailed explanation. Once the consent form has been signed, the patient’s inclusion visit will be carried out and all the variables will be measured (including the evaluation of the inhalation technique of all inhalers the patient uses). For eligible patients who decline to participate, basic information (age, sex, reason for declining) will be collected from the practice to allow examination of response bias.

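### Baseline inhalation technique is measured on every patient, but no planned effect analysis adjusts for it, and the multi-level models as written do not remove baseline imbalance

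*Protocol article*

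**What the plan says.** The Recruitment section for patients has all variables measured at the inclusion visit, "including the evaluation of the inhalation technique of all inhalers the patient uses". The primary outcome is binary: "We consider the correct inhalation technique to be used when all steps have been performed correctly". The covariates are given as a list in the section on first-level variables. It begins "Independent variables are age, sex, education level, co-morbidities, COPD diagnosis duration", continues with mental or cognitive status, and ends "types and number of inhalers, previous training received in use of the inhalation techniques and prescribed treatment for COPD". Baseline technique is not on it; previous training is the nearest item. The GP list (age, sex, education, guideline access) does not supply it either.

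Under Statistical analysis, General:
- For the primary outcome, "the between-group comparison for the primary outcome will be explored using the χ^2^ test", with risk reductions and NNT.
- For the rest, "Inferences for secondary outcomes will be made using ANOVA" or the χ² test.
- A logistic model follows, "considering the intervention as the predictive variable and the rest of the independent measures as the possible modifying factors".
- On balance, "The baseline comparison will be made between the main variables that we expect to be related to the primary outcome", again by χ² or ANOVA.

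Under Multi-level analysis, continuous outcomes get a mixed model with time and arm fixed and GP and patient random. Dichotomous outcomes get GEE of analogous structure. Neither names a baseline covariate or a time-by-group term.

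**The concern.** The baseline value of the outcome is often among its best predictors, and here it is in hand for every patient at no extra cost. With only 10 GPs per arm, chance can leave the arms visibly different in technique before any training. A test of baseline balance detects such a gap but does not correct for it. Two things are at stake: an estimate that moves with the baseline gap in this particular trial, and precision left unused.

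The multi-level section does not settle the matter. A model with main effects of time and arm only does not isolate the change after training.

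**Working it through.** The plan gives no figure for baseline adjustment, so there is none to reproduce. It also gives neither a baseline rate nor a baseline-to-follow-up correlation r. Results are therefore ranges under stated assumptions.

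**Inputs**
- From the protocol: 10 GPs per arm; 267 patients and 20 GPs, so 267/20 = 13.35 per GP; 40 % loss, so 13.35 × 0.6 ≈ 8 per GP retained; ICC 0.1 (assumed to apply at baseline too); target difference 25 points.
- Assumed: baseline proportion correct p = 15 % or 25 %, with 10 % as a check, because the Background reports more than 85 % incorrect use; r = 0.1 to 0.5.

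**1. Size of a chance baseline gap**

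SD = √{2p(1−p)[1+(m−1)ICC]/(10m)}

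- m = 13.35, bracket = 2.235: p = 0.15 gives √(2×0.1275×2.235/133.5) = 0.065; p = 0.25 gives √(2×0.1875×2.235/133.5) = 0.079.
- m = 8, bracket = 1.7: p = 0.15 gives √(2×0.1275×1.7/80) = 0.074; p = 0.25 gives √(2×0.1875×1.7/80) = 0.089.
- Check at p = 0.10, m = 13.35: 0.055.

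The 95 % limits (1.96 × SD) run from about ±13 to ±17.5 points for p = 15–25 %. The normal probability of a gap above 10 points is 13 % and 21 % for p = 15 % and 25 % with all enrolled patients, and 17 % and 26 % with those retained. At p = 10 % with all enrolled it is about 7 %.

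**2. How much reaches an unadjusted follow-up comparison**

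Shift ≈ r × gap (linear approximation, similar variability at both visits). For a 10-point gap: r = 0.1 gives 1 point, 0.3 gives 3, 0.5 gives 5. The shift is somewhat larger if technique varies more at follow-up than at baseline.

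**3. Precision**

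Variance factor ≈ 1 − r²: 0.99, 0.91 and 0.75 for r = 0.1, 0.3 and 0.5, a cut of 1 %, 9 % and 25 %. In patients: 267 × factor = 264, 243 and 200.

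**4. The multi-level model as written**

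If baseline is not a time level, it is unused. If it is, then with complete balanced data on a linear scale the arm coefficient is the average difference over visits. The logistic GEE behaves similarly, though not exactly.
- Baseline and 12 months, true effect 25 points, no gap: (0 + 25)/2 = 12.5.
- All four visits in the Abstract, the same effect at each follow-up: (0 + 3×25)/4 = 18.75.
- Two visits with a 10-point gap: the gap contributes (10 + 10r)/2, that is 5.5 to 7.5 points for r = 0.1 to 0.5, which is more than in step 2.

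This model therefore dilutes the effect and does not remove the gap.

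**The case against.** The strongest reply is that the multi-level section already covers this. Technique is measured at inclusion and at follow-up, so time most naturally includes baseline, and a condensed article may leave the time-by-group term to a fuller plan. It stands that baseline data may enter a model, and that a stated time-by-group contrast would answer much of the point. It does not stand that the text does so: the fixed effects are named and the contrast is not among them. The covariate list is likewise written out, so the omission is a stated choice and not silence.

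Second, the phrase about modifying factors need not mean interactions. The Discussion speaks of confounding factors to be considered in the analysis, so covariate adjustment is a fair reading. That is accepted, but baseline technique is still not one of those factors.

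Stronger readings are tempting, and the documents do not support them:
- A reader might infer that a baseline gap passes whole into the effect, or that the trial is biased. Only a fraction passes, and chance imbalance averages to zero over randomisations.
- A reader might infer a large, definite gain in power. That requires GP differences at 12 months to track those at baseline closely. No document says so, and the intervention aims to change GPs' practice.
- For the same reason a reader might want the GP's baseline proportion correct as a required covariate. Where GP differences do not persist, that term can cost precision with 20 clusters.

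**Conclusion.** The point holds as a moderate weakness in the analysis plan. No effect analysis in the General section conditions on baseline technique, and the multi-level models as written do not remove a baseline difference. If baseline is a time level, they also shrink the estimated effect.

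The chance gap has an SD of about 6 to 9 points against a 25-point target, assuming 15–25 % correct at baseline, ICC 0.1 and 8 to 13 patients per GP. It is smaller if fewer patients are correct at baseline. About 1 to 5 points of a 10-point gap carry over, and adjustment saves about 1 to 25 % of the variance, for r between 0.1 and 0.5. If r is near 0.1 the gain is trivial; near 0.5 it is worth about 67 of the 267 patients. The absence of bias in expectation refers to chance imbalance only. The Study limitations section itself notes that patients are recruited after GPs are randomised.

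**What to change.** In the cluster-adjusted primary model at 12 months, prespecify the patient's baseline technique as a covariate, either correct yes/no or the number of correct steps. The step count is likely to be more informative if few patients are fully correct at inclusion. Name this adjusted analysis as the effect analysis. Because the plan reports absolute risk reduction and NNT, derive these from the adjusted model as a standardised risk difference.

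For SGRQ, spirometry and dyspnoea, add the baseline value of the same measure as a covariate in the mixed models.

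The alternative is to keep baseline as a time level and state the time-by-group contrast as the treatment effect. If the arms are free to differ at baseline, that contrast is a comparison of changes. Its variance relative to the plain follow-up comparison is about 2(1−r): 1.8 at r = 0.1, 1.4 at 0.3 and 1.0 at 0.5. The covariate route is therefore preferable, or the model should give both arms a common baseline mean.

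The GP's baseline proportion need not be a required term. The cost is a few sentences of analysis wording, settled before outcome data are examined; no new data are needed.

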#### Multi-level analysis

ICCs will be determined and published for all primary outcome variables to assist future research. Potential confounders will be compared between groups to confirm that the randomisation has provided the appropriate balance.

The effect of the intervention on outcomes measured on a continuous scale (such as SGRQ score) will be estimated and tested using mixed model ANOVA in which time and treatment group will be fixed effects and GP and subject will be random effects. The effect of the intervention on the dichotomous variables will be analysed using generalised estimating equations with a logistic link and a model structure that is analogous to that described above.

### Study limitations

The first limitation is about the actual study design. In pragmatic cluster randomised controlled trials, the first bias to take into account is the selection bias, as the randomisation is usually applied in the second level, before recruitment of the first-level participants, which is where the intervention impact is measured. However, there are strategies that minimise this bias, and we are using these in this study. First, the selection and follow-up of patients (patient inclusion visit and visit 1) will be carried out by an external researcher who will have no knowledge of GP randomisation. Second, the effect of the intervention over recruitment can lead to different recruitment indexes, depending on the groups, due to the possibility that GPs in the control group could be less motivated to participate. Moreover, to avoid different recruitment indexes in both groups, once the trial is finished, the GPs in the control group will be trained in the same way as the study group professionals were trained (if the intervention shows a significant improvement in patients) [23, 32].

Another study limitation is the potential for loss to follow-up. To minimise these losses, patients will be contacted at least three different times and at different times of day. However, loss to follow-up was taken into account in the sample size calculation and will be taken into account in performing data analysis (intention-to-treat analysis).

Another bias is the Hawthorne effect, which relates to how participants in a study change their behaviour under observation. However, we believe that the effect of this bias will be minimal because of patients’ being trained and followed by their GPs, with the exception of the inclusion and final visits. Besides, there is a control group in which the follow-up will permit us to minimise the real impact of this bias.

There could be measurement bias due to mistakes in recording of some variables or interviewer bias due to the administration of the questionnaires. To minimise these biases, interviewers will have been trained previously to ensure that visits will be as homogeneous as possible. A DCF and a manual that explains how each variable is measured at the follow-up visits will be given to the GPs in the intervention group.

Finally, we point out that a rescue mechanism is contemplated for the control group. This mechanism will be applied when the patients perform critical errors in the inhalation techniques that compromise the totality of the drug deposition and its effect. This rescue mechanism can create an information bias which could change the effect of the educational intervention in this study. However, we must ensure the well-being of the patient. All adverse events will be reported on the DCF and will be taken into account in the post hoc analysis.

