##### Interventions in patients

The patients included in the intervention group will receive an educational intervention from their GPs, who will train them in the correct use of their devices. This intervention will consist of the following:Performance of inhalation techniques to detect mistakes that will be registered on a specially designed sheetDemonstration of proper inhalation techniquesIdentification of mistakes in technique and opportunities to ask health professionals about how to perform inhalation properly

The patients will be given an appointment for reinforcement visits at 3 and 6 months after the inclusion visit. In these visits, the GPs will encourage and refresh their performance of inhalation techniques.

As the educational intervention will not be blinded, the external researcher responsible for collection of patient data will not know the patient allocation. The patients included in the control group will follow the standard clinical practice.

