##### Interventions in GPs

The intervention consists of a demonstration of correct inhalation technique and the rationale for it to a group of two to four GPs. After the demonstration, the participants are asked to identify their mistakes and ask any questions they may have, which will be resolved until full understanding of the technique is achieved. The intervention will take approximately 15 minutes to deliver. Reinforcement with written information is provided via the patient’s data collection form (DCF), where the specific step-by-step schedule for each device is recorded at each patient’s visit (initial visit and at 3 and 6 months).

Blinding of the intervention for GPs will not be possible for either researchers or GPs. Table 1 provides a brief summary of the interventions for the first- and second-level participants.

**Table 1 Tab1:** Brief summary of interventions in first and second levels

	Second level: professionals (GPs)	First level: patients
Content	Inhalation technique workshop:	Inhalation technique workshop:
	• Step-by-step correct technique demonstration (how)	• Step-by-step correct technique demonstration (how)
	• Explanation of each step for each device (why)	• Explanation of each step for each device (why)
Who applies the intervention	Research team	GPs from the intervention group
Who receives the intervention	GPs from the intervention group	Patients with COPD from the intervention group

*COPD* chronic obstructive pulmonary disease, *GP* general practitioner

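### Adverse events are assigned to a form that the article describes only in connection with intervention GPs and their visits, so events would be sought more often in the intervention arm

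*Protocol article*

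**What the plan says.** The last paragraph of Study limitations deals with the rescue mechanism for control patients and ends with the only statement on adverse events: "All adverse events will be reported on the DCF and will be taken into account in the post hoc analysis". No other instrument for events is named.

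The DCF is described in two other places.

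- Study limitations, on measurement bias, gives its recipients: the form, with an explanatory manual, "will be given to the GPs in the intervention group".
- Interventions in GPs makes it part of the intervention: "Reinforcement with written information is provided via the patient’s data collection form (DCF"), and it is the place "where the specific step-by-step schedule for each device is recorded"; the timing given is the initial, 3-month and 6-month patient visits.

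On contacts, Interventions in patients says, after listing what the intervention group receives: "The patients will be given an appointment for reinforcement visits at 3 and 6 months after the inclusion visit". GPs run these visits to refresh technique. For the other arm the same section says: "The patients included in the control group will follow the standard clinical practice". The abstract, by contrast, gives patients four visits (baseline, 3, 6 and 12 months) without distinguishing the arms.

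According to the patient Follow-up section and Study limitations, the inclusion and final visits are run by a researcher unaware of the GPs' allocation, with no restriction by arm. The form used at those visits is not named.

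**The concern.** The word *all*, in a paragraph about control patients, shows that control-arm events are meant to be captured. Yet the form chosen for them is described only in connection with intervention GPs and the visits they hold as part of the treatment. The number of recorded events would then depend partly on how often patients are asked. The extra asking would fall in one arm and be done by clinicians who know the allocation.

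If the post hoc analysis compares arms, the intervention could appear to cause events that were merely better recorded. Events in control patients who continue with a faulty technique, a risk the rescue paragraph itself raises, would be under-recorded.

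The obvious repair has a problem of its own. The DCF carries the step-by-step technique material, so giving the same form to control GPs would pass part of the intervention to the control arm.

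**Working it through.** The article gives no event rate or capture figure to reproduce. The check is a count of contacts, followed by an illustration.

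**Step 1: contacts at which an event could be recorded, under three readings.**

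| Reading | Intervention | Control |
|---|---|---|
| A. DCF held by intervention GPs only | 3 (months 0, 3, 6) | 0 |
| B. The masked researcher also records events at inclusion and month 12 (not stated) | 4 (months 0, 3, 6, 12) | 2 (months 0, 12) |
| C. The abstract's four visits apply to both arms, with events recorded at each | 4 | 4 |

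Capture is unequal under A and B. It is equal only under C, and C conflicts with Interventions in patients, where the 3- and 6-month visits appear only as reinforcement of the intervention.

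**Step 2: size under reading B.** This is milder than A, because it credits controls with the 12-month visit. Assumptions, none from the article:

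- each contact after an event captures it with probability p = 0.3, 0.5 or 0.7;
- contacts are independent;
- events are spread evenly over 12 months;
- true rates are equal in the two arms.

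With k later contacts, the probability of capture is 1 − (1 − p)^k. In the intervention arm:

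- events in months 0–3 (25% of events) have k = 3;
- events in months 3–6 (25%) have k = 2;
- events in months 6–12 (50%) have k = 1.

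In the control arm k = 1 throughout, so capture equals p.

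Intervention capture = 0.25 × [1 − (1 − p)³] + 0.25 × [1 − (1 − p)²] + 0.5 × p

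- p = 0.3: 0.25 × 0.657 + 0.25 × 0.510 + 0.5 × 0.3 = 0.442. Ratio to control 0.442 / 0.30 = 1.47.
- p = 0.5: 0.25 × 0.875 + 0.25 × 0.750 + 0.5 × 0.5 = 0.656. Ratio 0.656 / 0.50 = 1.31.
- p = 0.7: 0.25 × 0.973 + 0.25 × 0.910 + 0.5 × 0.7 = 0.821. Ratio 0.821 / 0.70 = 1.17.

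**Step 3: where the excess arises.** For events in months 0–3 alone the ratios are 0.657/0.30 = 2.19, 0.875/0.50 = 1.75 and 0.973/0.70 = 1.39. For events in months 6–12 the ratio is 1, because each arm then has one later contact. The early-event figures are the extreme subset and should not be quoted as the overall size.

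**The case against.** The strongest reply is that the article does not confine the DCF to one arm. The sentence on who receives it is a safeguard against measurement bias and does not list every user. The form is called the patient's form. The promise about events sits in a paragraph on control patients, which suggests that they have one too. Masked assistants measure patients in both arms and must write the data somewhere. All of this stands. A reader might infer that the DCF goes only to intervention GPs, but the text does not say so.

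A reader might also infer that events in months 6 to 12 go unrecorded. The documents do not support that. The initial, 3- and 6-month timing is attached to the device schedule, not to every use of the form. A 12-month visit exists for patients in both arms, and the article is silent on whether events are asked about there. In a condensed article, that silence is no finding.

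Two further points also stand. Adverse events are not a listed outcome, and the article specifies no between-arm comparison, only that events will be considered post hoc. The capture probabilities are assumed.

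The stated route remains. The article goes beyond silence: it assigns all events to a named form, names intervention GPs as its recipients, and describes the intermediate GP visits for the intervention arm alone. Clarifying who else uses the form would not equalise the contacts unless the 3- and 6-month visits also take place in the control arm.

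**Conclusion.** The point holds as a problem of unequal ascertainment. As written, events are sought more often in the intervention arm, by unmasked GPs, and no recording route is described for control patients. A comparison of arms would tend to show more events under the intervention even with equal true rates. The excess is about 1.5-, 1.3- or 1.2-fold for p = 0.3, 0.5 or 0.7. These ratios rest on independent contacts, even timing of events and a 12-month recording contact in both arms, and they illustrate scale rather than predict it. If the intermediate visits take place in both arms with the same recording, the difference in contact frequency disappears.

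The consequence is limited to safety reporting. The primary outcome and the listed secondary outcomes are not affected. This is an improvement worth making, not a threat to the main result.

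**What to change.** 1. Reconcile the abstract, Interventions in patients, Interventions in GPs and both DCF statements in Study limitations. State which patients attend at 3 and 6 months, who completes a DCF in each arm, and who records events in the control arm.
2. Take between-arm event collection off the technique form. Have the masked research assistant complete the same short adverse-event form, without technique steps, for every patient in both arms at the existing 12-month visit, covering the whole period since inclusion.
3. Base any between-arm comparison of events on that form alone. List events found only at the intervention GPs' 3- and 6-month visits separately, without comparing arms.

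The cost is one extra page at a visit already planned, plus protocol wording. There are two drawbacks. The first is recall over 12 months. The second is that events are missed in patients lost before month 12, which matters here because the sample size section allows for 40% loss (0.40 × 267 ≈ 107 patients). A check of practice records in both arms could reduce both drawbacks. It should be optional, because the article describes the records search only for identifying eligible patients, and follow-up review would be extra work.
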